#### Treatment group

2.5.1.

Acupoints of Baihui (GV20), Shenting (GV24), Sishencong (EX-HN1), bilateral Benshen (GB13), Shangwan (CV13), Zhongwan (CV12), Xiawan (CV10), Qihai (CV6), bilateral Tianshu (ST25), bilateral Neiguan (PC6), bilateral Shenmen (HT7), and bilateral Zusanli (ST36) will be used in EA group (locations are shown in Table 1 and Figure 3). With participants in a prone position, acupuncturists will use 75% alcohol pads to sterilize the skin around the acupoints and then insert disposable needles into the acupoints. For Baihui (GV20), Shenting (GV24), Sishencong (EX-HN1), bilateral Benshen (GB13), the needles will be inserted approximately 5–10 mm with a 30° angle between the needle tip and the scalp, for Shangwan (CV13), Zhongwan (CV12), Xiawan (CV10), Qihai (CV6), bilateral Tianshu (ST25), bilateral Neiguan (PC6), bilateral Shenmen (HT7), and bilateral Zusanli (ST36). Needles will be inserted at an angle of 90° and a depth of 20–30 mm. Lifting and thrusting combined with twirling and rotating will be performed for at least 10 s per acupoint to reach the De qi sensation (soreness, numbness, distention, and heaviness). Then a pair of electrodes from the EA apparatus will be connected to the needle handles at Baihui (GV20), Shenting (GV24). The EA waveform adopts 2/100 hz density alternating wave and the intensity of electric current will be regulated until the participants can perceive and tolerate it. Immediately after needle removal, acupuncturists will gently press acupoints with dry sterilized cotton balls to avoid bleeding.

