### Interventions

2.5.

The style of acupuncture is based on traditional Chinese medicine principle, and acupuncture prescription has been developed from literature review [27] as well as the clinical practice. Each participant will be ushered by a research assistant to hospital bed, which will be screened off separately one-by-one by opaque curtains. No companion will be allowed to stay with the participants during the treatment period. Acupuncturists should have a Chinese medicine practitioner license with at least 2 years of experience, and two acupuncturists will be given trial-specific training, such as the selection of acupuncture points and the usage of EA apparatus in different groups at the program launching session to realize their role and job in this study. Each participant will be performed EA or sham EA by the same acupuncturist throughout the trial. Also, two acupuncturists will not tell anyone else about the treatment allocation, and they will be asked to communicate with participants as less as possible to avoid inadvertent unblinding.

Sterile disposable acupuncture needles (length, 25–40 mm; diameter, 0.25–0.30 mm; Hwato Brand, Suzhou Medical Appliance Factory, Suzhou, China) and EA apparatus (HANS-200A acupoint nerve stimulator, Nanjing Jisheng Medical Co, Ltd) will be used in both groups. EA apparatus will be connected right after needles are inserted into all acupuncture points, and will be retained for 30 min. All participants will receive the same treatment according to their group. Both the treatment and sham groups will consist of 12-session intervention over 4 weeks (three sessions per week, ideally every other day). Intervention will be discontinued if the participants have any serious adverse events. All participants will be informed that the current of EA may not be perceived by human.

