**Figure 3. F0003:**
[figure not shown]
Locations of acupuncture points used in electroacupuncture group. EX-HN1: Sishencong, GV20: Baihui, GB13: Benshen, GV24: Shenting, CV13: Shangwan, CV12: Zhongwan, CV10: Xiawan, CV6: Qihai, ST25: Tianshu, PC6: Neiguan, HT7: Shenmen, ST36: Zusanli.

**Table 1. t0001:** Locations of acupuncture points used in electroacupuncture group.

Acupoints	Location
GV20	On the midline of the head, 7 cun directly above the posterior hairline, approximately on the midpoint of the line connecting the apexes of the two auricles.
EX-HN1	A group of four points, at the vertex, 1 cun respectively posterior, anterior, and lateral to GV 20.
GV24	0.5 cun directly above the midpoint of the anterior hairline.
GB13	0.5 cun within the hairline of the forehead, 3 cun lateral to GV 24.
CV6	On the midline of the abdomen, 1.5 cun below the umbilicus.
CV10	On the midline of the abdomen, 2 cun above the umbilicus.
CV12	On the midline of the abdomen, 4 cun above the umbilicus.
CV13	On the midline of the abdomen, 5 cun above the umbilicus.
ST25	2 cun lateral to the center of the umbilicus.
PC6	2 cun above the transverse crease of the wrist, between the tendons of muscle palmaris longus and muscle flexor radialis.
HT7	At the ulnar end of the transverse crease of the wrist, in the depression on the radial side of the tendon of muscle flexor carpi ulnaris.
ST36	3 cun below ST 35, one finger breadth from the anterior crest of the tibia, in muscle tibialis anterior.

GV20: Baihui, EX-HN1: Sishencong, GV24: Shenting, GB13: Benshen, CV6: Qihai, CV10: Xiawan, CV12: Zhongwan, CV13: Shangwan, ST25: Tianshu, PC6: Neiguan, HT7: Shenmen, ST36: Zusanli.

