#### Compliance assessment

2.6.3.

Participants who achieve scores above 80 will meet the criteria for good compliance by the end of Week 4.

$$\text{Compliance score}=\frac{\text{Acutual treatment sessions}}{\text{Required treatment sessions}}x100$$

E.g. a participant undergoes 6 treatment sessions, as 12 sessions are required in this study, based on the equation, the compliance score amounts to 50, denoting inadequate compliance.

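### The 20–30 mm perpendicular needling rule also covers HT7 at the wrist crease; HT7 needs its own, shallower depth (a minor safety and intervention-accuracy point)

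*Protocol article*

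**What the plan says.** All of this is in the protocol article.

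- **Scalp points (section 2.5.1).** For GV20, GV24, EX-HN1 and bilateral GB13, "the needles will be inserted approximately 5–10 mm with a 30° angle between the needle tip and the scalp".
- **All other points (section 2.5.1).** The text lists CV13, CV12, CV10, CV6 and bilateral ST25, PC6, HT7 and ST36. A full stop then interrupts the sentence, and the next one reads: "Needles will be inserted at an angle of 90° and a depth of 20–30 mm".
- **Manipulation (section 2.5.1).** "Lifting and thrusting combined with twirling and rotating will be performed for at least 10 s per acupoint". No point is exempted.
- **Current (section 2.5.1).** Only one pair of points is stimulated electrically: "a pair of electrodes from the EA apparatus will be connected to the needle handles at Baihui (GV20), Shenting (GV24"). HT7 is therefore needled by hand only.
- **Location of HT7 (Table 1).** "At the ulnar end of the transverse crease of the wrist, in the depression on the radial side of the tendon" of flexor carpi ulnaris.
- **Needles (section 2.5).** "Sterile disposable acupuncture needles (length, 25–40 mm"; the text does not say which length is used at which site.
- **Uniformity (section 2.5).** "All participants will receive the same treatment according to their group".

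**The concern.** The protocol already varies depth by site: it treats the scalp differently from the rest of the body. It makes no such distinction for HT7. A point on the wrist crease, next to a tendon, gets the same perpendicular depth as the abdomen and as ST36, which Table 1 places in a leg muscle. The needle is then lifted, thrust and rotated.

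Two things are at stake. If the text is followed literally at HT7, the needle may pass through a large share of the wrist, which is potentially unsafe. If the acupuncturists go shallower there, the published intervention is wrong for those needles. The article calls itself the first standardized protocol for this use, so others may copy the stated depth.

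**Working it through.** **Step 1: which needles fall under the rule.** Counts follow from the point list in section 2.5.1 and from Table 1 (EX-HN1 is four points).

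- Scalp: GV20 1 + GV24 1 + EX-HN1 4 + GB13 2 = 8.
- Non-scalp: CV13, CV12, CV10 and CV6 4 + ST25 2 + PC6 2 + HT7 2 + ST36 2 = 12.
- Total: 8 + 12 = 20. HT7 is 2/20 = 10%.

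The 5–10 mm rule is defined by an angle to the scalp, so it cannot apply to HT7. Only the 20–30 mm rule remains, with or without the stray full stop.

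**Step 2: how often it applies.** With 12 sessions, each EA participant has 2 × 12 = 24 HT7 insertions. If all 30 attend every session, that is 24 × 30 = 720 of 20 × 12 × 30 = 7,200 insertions. This counts exposure, not harm.

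**Step 3: depth against wrist thickness.** The documents give no thickness. I assume 30–50 mm from palm side to back. Share = depth ÷ thickness:

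| Assumed thickness | 20 mm | 25 mm | 30 mm |
|---|---|---|---|
| 30 mm | 67% | 83% | 100% |
| 35 mm | 57% | 71% | 86% |
| 40 mm | 50% | 62.5% | 75% |
| 45 mm | 44% | 56% | 67% |
| 50 mm | 40% | 50% | 60% |

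**Step 4: break-even, with the same threshold of one half at both ends.**

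- 20 mm falls below half once the wrist exceeds 20 ÷ 0.5 = 40 mm, which is inside the assumed range.
- 30 mm falls below half only above 30 ÷ 0.5 = 60 mm, which is outside it.

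**Step 5: needle length.** Every needle in the 25–40 mm range can reach 20 mm. A 25 mm needle cannot reach 30 mm, so the upper end of the rule needs one of the longer needles.

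**The case against.** The strongest case against is that the documents contain neither an accepted depth for HT7 nor any local anatomy. A share of wrist thickness does not show which structure the needle meets. The percentages therefore cannot prove danger, and an acupuncturist who stops at 20 mm in a thick wrist complies fully while staying short of the middle. The sentence is also visibly garbled, and a condensed article may simply have lumped the sites together.

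Most of this stands. It limits the point to a conditional one, weaker at 20 mm, and makes a drafting slip a real possibility. It does not remove the point: the published rule covers HT7 and gives no shallower alternative.

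The safeguards also count. The acupuncturists are licensed and receive trial-specific training, haemorrhagic disease is an exclusion, points are pressed after needle removal, and adverse events are recorded after each session. These lower the practical risk but do not correct the stated depth.

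Four stronger readings are tempting, and the documents do not support them:

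- **That operators have no discretion.** The same-treatment sentence concerns uniformity between participants. It does not forbid choosing within 20–30 mm by site.
- **That bleeding or access injury is likely.** Section 2.5 gives heparin to all participants and lists fistulas and grafts among the accesses. It does not give the timing of heparin relative to needling, or the location of the access.
- **That PC6 is equally at fault.** It is under the same rule, but Table 1 places it above the wrist crease. The wrist-thickness check was not made for that site, so nothing is claimed there.
- **That the trial result is compromised.** The HT7 depth is part of what the EA arm receives. It changes neither the randomisation nor the response-rate comparison.

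**Conclusion.** The point holds as a minor safety and intervention-accuracy point on 2 of 20 manually needled sites. What the text says is certain: HT7 shares the 90°, 20–30 mm rule, with manipulation. Its implausibility at the wrist depends on the assumed 30–50 mm thickness. On that assumption, 30 mm is at least 60% of the wrist throughout, while 20 mm ranges from 40% to 67%. The concern is firm at the upper end, which a 25 mm needle cannot reach, and weaker at the lower end. That the practice would be potentially unsafe is a judgement; no injury rate can be derived from the documents.

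**What to change.** Take bilateral HT7 out of the 20–30 mm rule and give it a separate depth below 20 mm, chosen by the investigators. State whether the 10 s of lifting and thrusting applies there. Remove the stray full stop so that the list of points and its depth read as one sentence. The other 12 − 2 = 10 non-scalp needles can stay under the rule.

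Enrolment was due to finish in June 2024 and the article appeared on 29 April 2025, so recruitment may already be over. In that case, report the depth actually delivered at HT7 instead of rewriting the rule.

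The cost is one sentence and a short briefing of the two acupuncturists, or one line in the results report. Sample size and analysis do not change.

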**Figure 3. F0003:**
[figure not shown]
Locations of acupuncture points used in electroacupuncture group. EX-HN1: Sishencong, GV20: Baihui, GB13: Benshen, GV24: Shenting, CV13: Shangwan, CV12: Zhongwan, CV10: Xiawan, CV6: Qihai, ST25: Tianshu, PC6: Neiguan, HT7: Shenmen, ST36: Zusanli.

**Table 1. t0001:** Locations of acupuncture points used in electroacupuncture group.

Acupoints	Location
GV20	On the midline of the head, 7 cun directly above the posterior hairline, approximately on the midpoint of the line connecting the apexes of the two auricles.
EX-HN1	A group of four points, at the vertex, 1 cun respectively posterior, anterior, and lateral to GV 20.
GV24	0.5 cun directly above the midpoint of the anterior hairline.
GB13	0.5 cun within the hairline of the forehead, 3 cun lateral to GV 24.
CV6	On the midline of the abdomen, 1.5 cun below the umbilicus.
CV10	On the midline of the abdomen, 2 cun above the umbilicus.
CV12	On the midline of the abdomen, 4 cun above the umbilicus.
CV13	On the midline of the abdomen, 5 cun above the umbilicus.
ST25	2 cun lateral to the center of the umbilicus.
PC6	2 cun above the transverse crease of the wrist, between the tendons of muscle palmaris longus and muscle flexor radialis.
HT7	At the ulnar end of the transverse crease of the wrist, in the depression on the radial side of the tendon of muscle flexor carpi ulnaris.
ST36	3 cun below ST 35, one finger breadth from the anterior crest of the tibia, in muscle tibialis anterior.

GV20: Baihui, EX-HN1: Sishencong, GV24: Shenting, GB13: Benshen, CV6: Qihai, CV10: Xiawan, CV12: Zhongwan, CV13: Shangwan, ST25: Tianshu, PC6: Neiguan, HT7: Shenmen, ST36: Zusanli.

#### Sham group

2.5.2.

Twenty non-acupoints based on literature review [28,29] and the clinical practice will be used in sham group (locations are shown in Table 2 and Figure 4). Participants will use an opaque patch to cover their eyes and lie in a prone position, acupuncturists will use 75% alcohol pads to sterilize the skin around the acupoints and then insert disposable needles into the acupoints. Needles will be inserted at an angle of 90° and a depth of 2–3 mm (superficial penetration) in acupoints located in face and will be inserted at an angle of 90° and a depth of 2–3 mm in acupoints located in limbs and abdomen without any manipulation like lifting and thrusting or twirling and rotating to avoid De qi sensation. The sham electrodes from the EA apparatus will be connected to the needle handles at non-acupoint 1 (NA1) and NA2. The sham electrode lines will be identical to the real one, but the inner metal wires will be cut off. Therefore, no current will be outputted with the EA apparatus in a power-on state with a lighted power indicator and voice of clatter. The parameters of sham EA apparatus and treatment will be the same as in the EA group. Participants will be treated individually to avoid communication.

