We cautiously designed the present study according to relevant guidelines, the study adheres to well-established methodological requirements, including adequate randomization, allocation concealment, and blinding of participants, outcome assessors and statisticians, providing reliable evidence on the efficacy and safety of EA for insomnia in ESRD undergoing MHD. Specifically, we will evaluate beneficial effects of EA on sleep onset latency, wake after sleep onset, early morning awakening, total wake time, total sleep time, and sleep efficiency. We will use computer-produced randomization and allocation concealment from a third party to minimize selection bias and apply block randomization to ensure a balanced prognosis between intervention groups. Participants, data analysts, and outcome assessors will be blinded to group allocation. The allocation of all participants will be concealed until the statistical analysis is completed. All processes follow traditional Chinese medicine theory and clinical practice. Due to the increased nocturnal systolic BPV and inflammatory factors induced by insomnia in ESRD patients, we will adopt outcome measurements including 24-Hour ambulatory blood pressure and blood sample (plasma levels of C-reactive protein (CRP) and D-Dimer) to objectively investigate the effect of EA for insomnia in ESRD undergoing MHD. There will be 3 sessions each week during the 4-week treatment period, resulting in a total of 12 sessions with a 4-week follow up. The well-designed study can provide a profound impact on the clinical practice of EA for insomnia in ESRD undergoing MHD.

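### The eye cover is written only into the sham procedure and the adjustment of current to perception only into the EA procedure, contrary to the protocol's statement that sham treatment matches EA and at some risk to participant blinding

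*Protocol article*

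**What the plan says.** Section 2.5.2 (Sham group) opens its procedure with "Participants will use an opaque patch to cover their eyes and lie in a prone position". The parallel sentence in section 2.5.1 (Treatment group) reads "With participants in a prone position, acupuncturists will use 75% alcohol pads to sterilize the skin around the acupoints": the same position and skin preparation, with no eye cover. Section 2.5 (Interventions), which holds the measures common to both arms, does not mention one either.

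On the current, section 2.5.1 says "the intensity of electric current will be regulated until the participants can perceive and tolerate it". In section 2.5.2 the inner wires of the leads are cut, so that "no current will be outputted with the EA apparatus in a power-on state with a lighted power indicator and voice of clatter". The same section then states "The parameters of sham EA apparatus and treatment will be the same as in the EA group".

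Section 2.5 adds safeguards. Beds are described as places "which will be screened off separately one-by-one by opaque curtains", companions are excluded, acupuncturists are to talk as little as possible, and "All participants will be informed that the current of EA may not be perceived by human". The Discussion counts blinding among the trial's strengths: "Participants, data analysts, and outcome assessors will be blinded to group allocation".

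**The concern.** A sham arm should differ from the active arm only in the components under test. An eye cover is not a component of EA. In an insomnia trial, covering the eyes of one arm only could itself affect rest, or how the session is experienced, in a direction nobody can state in advance.

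The current-adjustment step is different in kind, because perceptible current belongs to the treatment being tested. The problem there is that the sham procedure describes no imitation of the adjustment, so the course of a session may differ visibly between arms.

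Both points bear on the primary result. The ISI is self-administered (2.6.1), so the participant is in effect the assessor. Blinding of outcome assessors and analysts (2.4) cannot protect that endpoint; only participant blinding can. If expectation differs between arms, it enters the response rate directly.

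**Working it through.** The plan states no figure on this point, so the check is a comparison of the texts.

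| Element | EA (2.5.1) | Sham (2.5.2) | Common text (2.5) |
|---|---|---|---|
| Position | prone | prone | not given |
| Eye cover | not mentioned | opaque patch | not mentioned |
| Needles | 1+1+4+2+1+1+1+1+2+2+2+2 = 20 | 20 | same needle type |
| Manipulation | at least 10 s per point, to reach De qi | none, to avoid De qi | not given |
| Current | adjusted until felt and tolerated | none | all told it may not be felt |
| Device | one electrode pair | look-alike leads, light and sound on | same apparatus, 30 min |
| Separation | not given | treated individually | curtains, no companions |

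**Step 1, eye cover.** Needle number, position, device and session length are matched. Manipulation, depth and current differ by design, because they are what the sham is meant to remove. The eye cover is the one listed difference with no such rationale. If it was worn for the whole 30-minute retention at all 12 sessions, exposure would be 12 × 0.5 h = 6 h. The article gives no wearing time, so that duration is an assumption.

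**Step 2, the sameness sentence.** Waveform and timing can be set identically on a device with cut leads. An intensity defined by what the participant feels cannot, because no current reaches the participant. As written, the sentence therefore does not cover the intensity step, and it conflicts with a cover given in one arm only.

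**Step 3, the information given to participants.** Telling everyone that the current may not be felt helps a sham participant who feels nothing. It does not help in the same way in the EA arm, where adjustment continues until the current is felt.

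**Step 4, illustration only.** Suppose EA has no specific effect and the unmatched elements alone raise the EA response rate. Inputs from the article are 30 per arm (2.7) and α = 0.025 with a Chi-squared test (2.8). Assumed inputs are a two-sided, uncorrected test, sham response of 20%, 30% or 40%, and the size of the bias. With x₁ and x₂ responders and pooled proportion p̄, z = [(x₁ − x₂)/30] / √[p̄(1 − p̄) × 2/30]. The test rejects when |z| > 2.24, and the rejection probability is summed over all binomial outcomes.

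| Assumed bias | Sham 20% | Sham 30% | Sham 40% |
|---|---|---|---|
| 0 points | 2.6% | 2.6% | 2.6% |
| +10 points | 9.0% | 7.8% | 7.7% |
| +20 points | 29.8% | 25.9% | 25.7% |

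If the eye cover instead helped the sham arm, the bias would run the other way and hide a benefit. The table shows how the test would respond to a bias; it is not evidence that one exists.

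**The case against.** The strongest reply is that silence is not a statement. Section 2.5.1 does not say that EA participants' eyes are uncovered. In a condensed article the patch may simply have been left out there, and the sameness sentence can be read as describing one shared routine. Likewise, section 2.5.2 does not rule out a mock adjustment. This stands in part: the documents do not establish what is actually done. The text still needs correcting under either reading, because a team following it would cover eyes in one arm only.

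A reader might go further and infer that blinding is broken, since the patch gives the arm away. The documents do not support that. A participant sees only their own arm and would have to know both procedures to use the patch as a clue. Curtains, individual treatment, look-alike leads, the light and sound of the device, and the neutral information all work against disclosure. Participants do come from one hemodialysis department (2.2), so contact outside sessions is possible, but that is a risk and not a demonstrated failure.

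A reader might also treat the felt current as a difference unrelated to EA. It is part of EA; only the lack of a matching sham step is at issue. Nor is the absence of a described blinding check an error here, since that may sit in the full protocol. Finally, the limitations in the Discussion already concede that unblinded acupuncturists may attend more to the EA group. That deserves credit, but it covers neither the eye cover nor the adjustment step.

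**Conclusion.** The point holds in a limited form. As written, the eye cover belongs to sham alone and adjustment to perception to EA alone, with no sham counterpart described. This conflicts with the statement that sham parameters and treatment equal those of EA. It introduces one non-EA difference and puts participant blinding of a self-rated primary outcome at risk, despite genuine safeguards.

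No size of bias can be derived from the documents, and the net direction is unknown. The conclusion assumes that the procedures are delivered as the article describes them. If the patch was merely omitted from the EA section and a mock adjustment is already used, the remaining defect is one of description.

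**What to change.** Reconcile sections 2.5.1 and 2.5.2 so that eye covering is the same in both arms, whether used or not, and state it once in section 2.5. Describe one scripted device-adjustment routine for both arms. In sham it would be a mock adjustment, worded neutrally and consistently with the information already given to all participants, so that the exchange does not itself prompt suspicion. Reword the sameness sentence to say which settings are matched and which differ by design.

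Recording one treatment guess per participant and reporting it by arm would be an inexpensive optional addition; its absence is not an error.

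Section 2.2 expected enrolment to end in June 2024 and the article appeared in April 2025, so sessions may already be complete. If they were delivered as written, report the asymmetry as a limitation and temper the participant-blinding claim in the Discussion. For sessions still to come, the cost is a change of procedure wording, brief training of the two acupuncturists and slightly longer sessions.
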